## Abstract

**Background:**

Gay and bisexual men (GBM) are a major risk group for HIV acquisition, yet the majority of higher-risk GBM test for HIV less often than recommended (3–6 monthly). HIV self-testing has the potential to increase testing frequency and improve awareness of personal HIV status. HIV self-tests have been approved in some countries, however there are concerns whether self-testing would increase HIV testing frequency enough to compensate for the reduced sensitivity of self-tests in early infection. We describe here a randomised controlled trial to assess the effectiveness of self-testing in increasing HIV testing frequency among higher-risk GBM, and its acceptability.

**Methods/design:**

Participants are higher-risk HIV negative GBM (>5 partners or condomless anal intercourse in previous 3 months; n = 350), including 50 GBM who tested for HIV over two years ago or never tested before (‘infrequent-testers’). Participants are recruited from sexual health clinics and community-based organisations, and randomised 1:1 to either self-testing or standard-care (routine clinic-based testing) arms. The trial employs a wait-list control design: participants in the standard-care arm switch to self-testing arm in the second year, and gain access to self-test kits. Participants in the self-testing arm receive four oral-fluid self-test kits at enrolment, with additional kits provided on request. Demographics, sexual behaviour and HIV testing preferences are collected at baseline, and the frequency and pattern of HIV and sexually transmissible infection (STI) testing is collected via online 3-monthly questionnaires. The acceptability of self-testing is assessed at 12 months via an online questionnaire and in-depth interviews. A 24-h telephone support is provided, with expedited follow-up of those with reactive self-test results. The primary outcome is HIV testing frequency (mean number of HIV tests per person) over 12 months, and the secondary outcomes are: mean number of STI tests (chlamydia, gonorrhoea, syphilis) per person; reasons for HIV testing; and acceptability of HIV self-testing.

**Discussion:**

This is the first trial to evaluate the use of self-testing among GBM in Australia, and the first internationally among infrequent testers. The study will provide evidence on whether self-testing increases HIV testing frequency, and its acceptability among GBM. The findings will improve our understanding of self-testing patterns, and whether GBM supplement or replace their existing testing routine.

**Trial registration:**

Australian and New Zealand Clinical Trial Registration number: ACTRN12613001236785, registered on November 12, 2013.

## Background

Gay and bisexual men (GBM) are a major risk group for HIV acquisition, and are disproportionately affected by HIV in many countries [1]. The rates of HIV diagnoses among GBM in high income countries including the United States (US), United Kingdom (UK), and Australia have increased over the past decade [2–5]. In Australia, annual HIV diagnoses have increased by about 70 % since 1999, and over two-thirds of new infections are diagnosed in GBM [5].

Regular testing is recognised as a key strategy for HIV control. Reduction in risky sexual practices as a result of the awareness of one’s HIV-positive status [6–8], and early initiation of antiretroviral therapy, can substantially reduce the risk of HIV transmission to sexual partners [9–11]. Mathematical modelling suggests that earlier diagnosis and treatment of HIV-positive individuals could substantially reduce population incidence [12]. A recent trial also confirmed individual benefits with early initiation of antiretroviral therapy [13]. Clinical guidelines in many countries recommend that sexually active GBM should have at least annual HIV testing, with 3–6 monthly testing for higher-risk men [14].

HIV testing uptake among GBM in many middle and high income countries is lower than the recommended level [15–19], and less than a quarter of higher-risk Australian GBM test every 3–6 months consistent with the guidelines [20]. Between 8 and 34 % of HIV-positive GBM in Australia [21, 22], New Zealand [23], US [24, 25], UK [18], and Canada [26] are unaware of their HIV-positive status. Mathematical modelling suggests that individuals with undiagnosed HIV infections contribute disproportionately to HIV transmission [27, 28]. A number of barriers to frequent HIV testing among GBM have been identified, including: perceptions of being at low risk, fear of an HIV-positive diagnosis, no symptoms or illness, and structural barriers such as the need to return to clinics for test results, facing difficulties with appointments, lack of time, and the cost and inconvenience associated with attending clinics [17, 29, 30].

HIV self-testing has the potential to increase testing uptake among GBM by overcoming some of the impediments to testing, particularly structural factors, improve awareness of personal HIV-status, and give a greater sense of control over men’s own health [31, 32]. HIV self-testing kits have been approved for sale in the US [33] and UK [34], and other countries including France and Kenya have also changed regulations to allow self-testing for HIV [33]. Australian HIV testing policy was changed in July 2014 to support self-testing for HIV, allowing manufactureres to submit applications to the Therapeutics Goods Administration for approval of self-tests [35], however no self-tests have yet been approved for sale.

Surveys of GBM in Australia [36–40] and overseas indicate that men are highly interested in accessing self-testing if available [17, 41–46], and likely to increase their HIV testing frequency [47]. However, concerns remain about errors in interpreting test results by users, relatively lower sensitivity in early infections, emotional consequences of reactive results and access to counselling, impact on STI testing frequency, and linking people diagnosed with a self-test to care [32, 48, 49]. HIV self-testing has been found to be highly acceptable in a range of settings and populations [50–52], with little or no evidence of harm associated with self-testing (including anxiety, fear, worry, suicide, or harm as a result of false results) [53]. A high proportion of GBM in observational self-testing studies report that self-testing is easy to perform, and express willingness to test again using self-tests [54–58]. Almost all individuals (96 %) diagnosed with HIV in an unobserved field evaluation of oral fluid self-testing in the US said they would access follow-up confirmatory testing [59].

An oral fluid self-test (the OraQuick In-Home HIV Test) was approved in the US on public health grounds despite its relatively lower sensitivity in the field trials [32], and acute HIV infections [60]. It was estimated that in the first year of its availability, 2.8 million people in the US would use the OraQuick In-Home HIV Test, and even though there would be 3800 false-negative test results (missed infections), this would be offset by 45,000 new infections being detected. Overall a reduction of more than 4000 new HIV transmissions in the first year was estimated [32]. However, a subsequent modelling study predicted that if used by GBM in Seattle, HIV prevalence would increase as men would replace conventional laboratory tests at clinics with a less sensitive self-test [61]. It is worth noting that the model had important limitations, for example, not including men who had not tested before and assuming men would replace their routine testing with self-tests rather than any supplementation [62]. A recent analysis based on the Australian epidemic demonstrated that there would be a public health benefit (detection of HIV infections that would have otherwise remained undiagnosed) from self-testing if higher-risk GBM supplemented clinic-based testing using the OraQuick self-test or previously untested GBM used a self-test [63].

To date, there is evidence from only one, as yet unpublished, randomised controlled trial (RCT) in Seattle that access to HIV self-testing increases HIV testing frequency among GBM [47]. However, to our knowledge, no studies have specifically evaluated the use of HIV self-testing in GBM who test relatively infrequently or have never tested before. We describe here a randomised controlled trial which aims to assess the effectiveness and acceptability of HIV self-testing in higher-risk GBM who test more frequently (last HIV test within the past two years) and less frequently (last HIV test over two years ago or never tested before).

## Methods

### Study design

This is a non-blinded wait-list control RCT with individuals randomised in a 1:1 ratio to two study arms: intervention (HIV self-testing) arm; and control (standard-care) arm. Participants in each arm will be followed-up for two years. Participants in the standard-care arm will switch to the self-testing arm after one year of follow-up and get access to self-testing in the second year (Fig. 1).

**Fig. 1 Fig1:**
[figure not shown]
Trial overview

### Participants

Participants include two testing subgroups: those who had their last HIV test within the past two years (hereafter called ‘frequent testers’) and those who had their last HIV test over two years ago, or have never tested before (hereafter called ‘infrequent testers’).

### Study objectives

The primary objective of this trial is to compare HIV testing frequency between the self-testing and standard-care arms. The secondary objectives are to compare the frequency of sexually transmissible infection (STI) testing including chlamydia, gonorrhoea and syphilis between the two study arms; and to assess the reasons for HIV testing and acceptability of HIV self-testing in the self-testing arm.

### Study duration

The study will require 3 years to complete: 6 months for recruitment, 24 months to complete the follow-up and data collection, and 6 months for analysis and reporting.

### Ethical considerations

The study protocol has been approved by the South Eastern Sydney Local Health District Human Research Ethics Committee (HREC) and the Alfred Hospital HREC. Additional ethical approvals have been obtained from Victorian AIDS Council Research Promotion and Ethics Committee, and ACON Research Ethics Review Committee.

### Inclusion and exclusion criteria

Participants are eligible if they: identify as gay or bisexual men; are aged 18 years or above; are HIV negative (either self-reported or based on clinical records); plan to live in Australia for the next 2 years; and report any condomless anal intercourse, or >5 male sexual partners in the past 3 months. The eligibility criteria are adopted from Australian clinical testing guidelines to recruit higher-risk GBM [64], as they have the highest HIV incidence in Australia [65]. Participants are excluded if they: cannot speak and/or read English; cannot provide written consent; or are unwilling or unable to comply with all the requirements of the study.

### Recruitment

Participants are recruited from large urban sexual health centres and community-based organisations in Sydney, Melbourne and Cairns, including: Sydney Sexual Health Centre, Melbourne Sexual Health Centre, Cairns Sexual Health Service, ACON Sydney (the largest gay men’s health organisation in New South Wales), and the Victorian AIDS Council, Melbourne. Promotion of the study occurs through gay media, the study website [66] and websites of participating organisations, social media (Facebook), advertisements on Grindr (a mobile device social networking application for GBM), and posters and postcards at recruitment sites. Potentially eligible participants are informed about the study by recruitment staff and clinicians. The clinical sites also use other strategies for engaging potential participants, for example: eligible participants receive a prompt when they complete a computer-assisted self-interview for routine data collection; and study nurse receives an SMS (text message) when an eligible patient completes a computer-assisted self-interview. Participants are also able to express interest in the study by completing an online form via the study website. The study coordinator assesses the information provided and refers eligible participants to the recruitment sites.

All participants are required to attend one of the study sites for recruitment. A dedicated study nurse at each clinic or a designated staff member at the community sites confirms participants’ eligibility via routinely collected data on sexual behaviour or by using a paper-based eligibility screening template. Those eligible are given an information sheet, and the study procedures are explained to them. It is emphasised that the self-test is not recommended for use within three months of a potential exposure or risk event (the window period), and that reactive self-test results must be confirmed by a conventional laboratory test at a clinic. Participants are required to sign a written informed consent at recruitment covering all trial procedures and data collection.

### Randomisation

Computer-generated randomisation codes, stratified by testing group (frequent and infrequent testers), are produced by a biostatistician and sealed in opaque envelopes by a research assistant not associated with the trial. Once written consent is obtained, the recruitment staff select the next randomisation envelope according to the participant’s testing group and inform the participant of the study arm they are being assigned to – the self-testing or standard-care arm.

### Blinding

Given the nature of the intervention, it is not feasible to blind the recruitment staff and participants to their study arm allocation. However, recruitment staff are unaware of the allocation until the envelope is opened in front of the participant. The statistician analysing RCT data will be blinded to the study arms.

### Study procedures

#### Intervention (self-testing) arm

Participants randomised to the self-testing arm have access to oral fluid HIV self-test kits in addition to the usual clinic-based HIV/STI testing and care. At enrolment, participants in the self-testing arm receive four self-test kits including the manufacturer-supplied step-by-step instructions and a web-link to an instructional video. Four self-test kits provide a 12 month supply for higher-risk men who test every 3–6 months consistent with the guidelines [64]. Participants are able to request additional kits, one at a time, for a maximum of 12 kits in one year in case repeat testing is needed or men test more frequently in relation to risky sexual behaviour. Depending on participants’ preference, additional self-test kits are either picked-up from the study sites or sent by post in plain packaging. At the beginning of the second year of follow-up, all participants (including those switching from standard-care to the self-testing arm) are eligible to collect four self-test kits from study sites, or sent by post if requested. A central log of kits dispatched is maintained to keep track of the number of kits supplied to each participant. No training on performing self-tests is provided at baseline to mimic a real-world scenario where untrained individuals will purchase self-test kits over-the-counter from pharmacies or online.

##### HIV self-testing kits

The US Food and Drug Administration approved ‘OraQuick In-Home HIV test’ (OraSure Technologies Inc., Bethlehem, PA, USA) is being used for HIV self-testing in this study (Fig. 2). It is a second generation test which detects HIV 1/2 antibodies in oral fluid specimens. The specimen is obtained by swabbing the upper and lower gums using a collector device which is then transferred to a solution, and the results are read in 20–40 min [59]. The sensitivity and specificity of the OraQuick self-test in the hands of untrained users is 91.7 % (95 % confidence interval [CI]: 84.2-96.3 %) and 99.9 % (95 % CI: 99.9-100.0 %), respectively [59]. Every OraQuick kit is accompanied by step-by-step graphic and written instructions and two booklets with general information on HIV testing and interpretation of results. The manufacturer-specified window period for OraQuick self-test is three months [59], however published data show that second generation antibody immunoassays detect HIV antibodies within 25–35 days after HIV infection [67, 68]. The OraQuick self-test is a preliminary test and all reactive results must be confirmed with a conventional laboratory test. As the test kit is packaged for the US market, each self-test kit supplied to participants is prominently labelled with Australian telephone numbers for support and emergencies.

**Fig. 2 Fig2:**
[figure not shown]
OraQuick In-Home HIV Test kit contents: instruction booklet (flipchart design), specimen collection device, developer solution vial, pre-test and post-test information booklets, pencil, and disposal bag (Source: http://www.oraquick.com)

##### Telephone support lines

A 24-h telephone support line staffed by the study coordinators on a rotation basis is available to participants, providing support for the use of self-test kits, interpretation of results, and advice for reactive home test results. In addition, participants have access to existing telephone support lines of participating sexual health centres. A log of calls to the telephone support lines is maintained and the reason for each call is recorded.

##### Follow-up of reactive self-tests

Participants are advised to inform the study coordinator of any reactive self-test results. The responses to 3-monthly online questionnaires (see below) are also monitored for any reported reactive self-test results. Any participant with a reactive self-test result is advised by the study coordinator to undergo confirmatory laboratory testing and offered expedited clinical review and supportive counselling at the study clinics. If they prefer to go to a clinic other than the study clinics, they are offered assistance in arranging an appointment. The laboratory confirmation and management of participants with confirmed HIV diagnoses will be based on the standard protocols at the respective clinic, however their study involvement will cease.

#### Control (standard-care) arm

Participants randomised to the standard-care arm continue to access routine clinic-based HIV/STI testing and care at their preferred clinic, including clinics other than the study clinics. In Australia, most laboratories use fourth generation HIV screening immunoassays [69]. Supplementary HIV antibody, HIV p24 antigen, and Western Blot testing are performed on specimens that are reactive by the screening assay, and deemed positive if consistent with the national case definition [70]. After 12 months, participants in the standard-care arm switch to the self-testing arm and follow the same procedures as the self-testing arm.

### Outcome measures

The primary outcome is the mean number of HIV tests per person over 12 months. The secondary outcomes are: the mean number of STI (chlamydia, gonorrhoea, syphilis) tests per person; reasons for HIV testing; and the acceptability of HIV self-testing.

### Data collection

#### Clinical data

HIV and STI testing data for the duration of the study will be extracted from the patient management system for all participants recruited at study clinics.

#### Surveys

##### Baseline

All participants complete a self-administered online survey on a handheld electronic device at enrolment. The survey covers socio-demographics, sexual risk behaviour, HIV/STI testing history, attitudes to HIV self-testing, opinions about treatments for HIV, and an HIV testing self-efficacy scale measuring gay men's confidence in their ability to undertake HIV testing [71].

##### 3-monthly

Participants in both arms of the study complete a brief online survey every three months asking the number, location, reasons for, and results of HIV self-tests and HIV/STI tests at clinics and community sites, and sexual risk behaviour since their last survey. Participants are also asked about the number of self-test kits they used to test their sexual partner(s) or gave to someone else to test at another time. If participants report episodes of HIV/STI testing at clinics other than study clinics, those clinics are contacted to obtain test results. Consent for release of results is obtained at enrolment and mailed/faxed to relevant clinics when obtaining results.

##### 12 months

At 12 months, a survey is conducted including the same questions as the 3-monthly survey with some additional questions about self-testing acceptability, ease of use overall and for various steps of HIV self-testing, participants’ experience using self-tests to test themselves and their partner(s), if relevant, and their preferences for accessing and using HIV self-testing in the future.

#### Survey reminders

If participants have not completed a survey, they are sent up to three reminders via email or SMS, each one week apart. If surveys are not completed after three reminders, participants are sent a final SMS asking the total number of HIV tests and the number of HIV self-tests since their last survey.

#### In-depth interviews

About 25 participants in the self-testing arm will be invited to participate in a face-to-face semi-structured in-depth interview at the completion of 12 months follow-up. Participants are asked at enrolment if they are willing to be contacted for in-depth interviews. The interviews will focus on collecting detailed information about their HIV testing pattern prior to the study, their experience using self-tests to test themselves and their partner(s) during the study, any changes in their testing patterns and sexual behaviour after getting access to self-testing, and their opinions about HIV self-testing in the future. Participants from each of the following groups will be interviewed: those who tested themselves using self-tests only; those who tested at clinics and supplemented their testing with self-tests; those who tested their partner(s) using self-tests; and those who had a confirmed positive or false-reactive self-test result.

### Sample size

In the analysis, we intend to assess the primary outcome for the frequent and infrequent testers subgroups and overall. For frequent testers, a sample size of 112 in each arm will detect an increase in HIV testing frequency from 1.5 tests per year to 2 tests per year (standard deviation [SD]: 2.4) with 80 % statistical power and type I error probability of 0.05. The frequency of 1.5 tests per year is based on the results of a previous clinic based RCT in Melbourne [72], and data from Australian sexual health clinics [73]. For infrequent testers, a sample size of 14 in each arm will detect an increase in HIV testing frequency from 0.2 tests per year (assuming one HIV test in the past five years based on clinic data [73]) to 1 test per year (SD: 0.7) with 80 % statistical power and type I error probability of 0.05. On this basis, we conservatively estimate a sample size of 300 frequent testers and 50 infrequent testers for an overall sample size of 350. The sample size of 350 will achieve at least 80 % statistical power to detect an overall increase from 1.5 to 2 tests per year (SD: 2.4) for the two groups combined.

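### The 80% power stated for frequent testers and for the whole trial does not follow from the printed difference of 0.5 and SD of 2.4; at least one printed input is misstated

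*Protocol article*

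**What the plan says.** All of the relevant figures are in the Sample size section of the protocol article.

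- **Frequent testers:** the text reads "a sample size of 112 in each arm will detect an increase in HIV testing frequency from 1.5 tests per year to 2" (unit: HIV tests per person-year). The SD given is 2.4, and the claim is made "with 80 % statistical power and type I error probability of 0.05".
- **Infrequent testers:** 14 per arm for 0.2 to 1 test per year, SD 0.7, with the same power and type I error.
- **Planned size:** "we conservatively estimate a sample size of 300 frequent testers and 50 infrequent testers for an overall sample size of 350".
- **Whole trial:** 350 men are said to give at least 80% power "to detect an overall increase from 1.5 to 2 tests per year (SD: 2.4) for the two groups combined".

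The Study design section gives 1:1 allocation, and the Statistical analysis plan section names a t-test for comparing mean testing frequency. The article does not say whether the type I error is one- or two-sided.

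**The concern.** A difference of 0.5 with SD 2.4 is a standardised effect of 0.5/2.4 = 0.21. An effect that small normally needs several hundred participants per arm, so 112 per arm looks far too few, and 175 per arm looks too few for the overall claim as well.

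The statement concerns the primary outcome, in the larger subgroup and overall. If both the 0.5 and the 2.4 are right, a true effect of the planned size would be missed more often than not in frequent testers, and about half the time overall. A non-significant result could then be misread as evidence that self-testing does not raise testing frequency.

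**Working it through.** **Inputs (Sample size section unless noted).** Difference 0.5 (2 minus 1.5); SD 2.4; alpha 0.05; target power 80%; 112 per arm stated; 300 + 50 = 350 planned, so 150 frequent testers per arm and 175 men per arm overall (1:1 allocation, Study design). Two-sided alpha is assumed; one-sided is shown too.

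**Attempt to reproduce 112.** Normal approximation, n per arm = 2 × (1.960 + 0.842)² × (SD/difference)²:

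- 2 × 7.849 × (2.4/0.5)² = 15.70 × 23.04 = 361.7, so 362 per arm. The noncentral t gives 362.6, so 363.
- One-sided: 285 by normal approximation, 286 by t.

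The stated 112 does not reproduce.

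**Power at the stated and planned sizes.** Noncentrality = 0.5 / (2.4 × √(2/n)); power from the noncentral t with 2n − 2 degrees of freedom.

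| n per arm | Noncentrality | Two-sided power | One-sided power | Difference detectable at 80% (two-sided) |
|---|---|---|---|---|
| 112 (stated) | 1.56 | 34% | 46% | 0.90 |
| 150 (all frequent testers) | 1.80 | 44% | 56% | 0.78 |
| 175 (all 350) | 1.95 | 49% | 62% | 0.72 |

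**Cross-check on infrequent testers.** 15.70 × (0.7/0.8)² = 12.02, so 13 by normal approximation; the t-based value is 13.05, so 14. Power at 14 per arm is 83%. The stated figure reproduces, so the standard method works in the same paragraph and the mismatch is confined to the frequent-tester and overall statements.

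**What would give 112.** Each route changes a printed input:

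- SD about 1.33, difference 0.5, two-sided: 15.70 × (1.33/0.5)² = 15.70 × 7.076 = 111.1, so 112. One-sided, the SD would be about 1.5.
- Difference 0.9, SD 2.4, two-sided: 15.70 × (2.4/0.9)² = 15.70 × 7.111 = 111.6, so 112 (112.6 by t).
- Poisson variances (1.5 and 2) in place of the SD: 7.849 × 3.5/0.25 = 109.9, close to 112, but the printed SD is then not used.
- Reading 2.4 as a variance does not work: 151 two-sided or 119 one-sided by normal approximation.

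For the overall claim, 80% two-sided power at 175 per arm and a difference of 0.5 would need an SD of about 1.66 or less.

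**Side note: combined means.** Weighting the two strata gives:

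- Control mean (300 × 1.5 + 50 × 0.2)/350 = 1.31; self-testing mean (300 × 2 + 50 × 1)/350 = 1.86; difference 0.54.
- Control variance: (6/7)(5.76) + (1/7)(0.49) + (6/49)(1.3²) = 5.21. Self-testing variance: (6/7)(5.76) + (1/7)(0.49) + (6/49)(1.0²) = 5.13. Average 5.17, so SD about 2.27.
- Two-sided power at 175 per arm: about 61%.

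The printed combined 1.5 to 2 therefore does not match the stratum assumptions, but the matching inputs still fall short of 80%.

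**The case against.** The strongest reply is that this may be a reporting error and not a shortage of participants. If the calculation used an SD of about 1.33, 112 per arm is right, and power with a difference of 0.5 is about 90% at 150 per arm and 94% at 175 per arm. If the difference used was 0.9 with SD 2.4, power at the planned sizes is much the same, for that larger effect. Even if 2.4 is a variance, power is about 80% at 150 per arm and 85% at 175, although 112 still does not reproduce. This stands: the article shows that the inputs and the power claim are incompatible, not which of them is wrong.

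A reader might infer that the SD or the sample size must be the error. The documents do not support that, because a difference of 0.9 with the printed SD also gives 112.

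The combined-means inconsistency also does not inflate the overall claim. The printed 1.5 to 2 is the less favourable assumption (49% against 61%), so this point is secondary.

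None of this rescues the text as printed. One-sided testing reaches only 62% with all 350 men, the pair 0.5 and 2.4 is used for both claims, and nothing elsewhere in the article reconciles them.

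**Conclusion.** Both 80% power statements are wrong as written. On the printed inputs, 80% power needs 363 per arm against the 112 stated, and the planned enrolment gives about 44% power in frequent testers and 49% overall. These figures assume a two-sided t-test, equal allocation, a common SD and no drop-out; losses would lower them.

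A reader might go further and conclude that the trial is underpowered. That does not follow, because it requires both 0.5 and 2.4 to be the intended values, and the article does not establish this. What is established is that the SD, the difference or the sample size is misstated, and that the paragraph cannot be relied on until it is known which.

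**What to change.** Check the difference, the SD and the 112 against the original calculation and the source data, and state whether alpha is one- or two-sided. Then:

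- **If the SD or the difference was misprinted:** correct it, show its source, and recompute power for the planned 300 frequent testers and 350 overall.
- **If 0.5 and 2.4 are right:** restate two-sided power as about 44% for frequent testers and 49% overall, or as 80% power for differences of about 0.78 and 0.72 tests per year, before drop-out. Remove the word describing the size as conservative.

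As optional tidying, make the combined means follow from the strata (1.31 to 1.86, SD about 2.27), which gives overall power of about 61% if the stratum inputs are confirmed.

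The cost is a look at the original calculation and the rewording of one paragraph. No extra participants are needed for the correction. If the printed inputs are confirmed, the cost is a less favourable power statement.
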